## Abstract

**Background:**

Activities embedded in academic culture (international conferences, field missions) are an important source of greenhouse gas emissions. For this reason, collective efforts are still needed to lower the carbon footprint of Academia. Serious games are often used to promote ecological transition. Nevertheless, most evaluations of their effects focus on changes in knowledge and not on behaviour. The main objectives of this study are to 1) Evaluate the feasibility of a control and an experimental behaviour change intervention and, 2) Evaluate the fidelity (the extent to which the implementation of the study corresponds to the original design) of both interventions.

**Methods:**

People employed by a French research organisation (N = 30) will be randomised to one of the two arms. The experimental arm consists in a 1-hour group discussion for raising awareness about climate change, carrying out a carbon footprint assessment and participating to a serious game called “Ma terre en 180 minutes.” The control arm consists of the same intervention (1h discussion + carbon footprint assessment) but without participating to the serious game. On two occasions over one month, participants will be asked to fill in online surveys about their behaviours, psychological constructs related to behaviour change, sociodemographic and institutional information. For every session of intervention, the facilitators will assess task completion, perceived complexity of the tasks and the perceived responsiveness of participants. Descriptive statistics will be done to analyse percentages and averages of the different outcomes.

**Discussion:**

Ma-terre EVAL pilot study is a 1-month and a half pilot randomised controlled trial aiming to evaluate the feasibility and the fidelity of a 24-month randomised controlled trial. This study will provide more information on the levers and obstacles to reducing the carbon footprint among Academia members, so that they can be targeted through behaviour change interventions or institutional policies.

## Background

Reducing greenhouse gas emissions to successfully mitigate climate change is a great challenge of the 21st century. From demand-side perspective, an important percentage of greenhouse gases (72%) are related to household or “lifestyle” consumption such as housing, mobility and daily diet [1]. For this reason, citizens and communities are encouraged to change their behaviours and practices to mitigate climate change not only in their individual spheres but also in their professional and collective spheres [2]. If humanity wants to limit global warming to 1.5° (or 2°), a set of coordinated actions between citizens, investors, consumers, role models and professionals is needed [3].

Academia members, which include scholars, technical and administrative staff working in universities and research centres, are not exempt from contributing to greenhouse gas emissions and inequalities through certain behaviours. One common practice is attending in-person scientific conferences and field missions, which have been identified as significant sources of emissions [4]. Related to the Covid-19 lockdowns, many recent studies focused on conference habits in the academic sector. For example [5], compared the impact of three in-person conferences in the United States, Korea and England, and estimated that each academic attending to one of these three conferences produced between 1.3 and 1.8 tons of CO2e.

Moreover, research indicates that certain groups within academia face additional disadvantages in accessing in-person conferences. Women, individuals with household responsibilities, those requiring visa applications, scientists working in the Global South and early-career researchers are among those disproportionately affected [6–10].

Criticism has been raised both within and outside academia regarding the high emissions associated with such behaviours [11, 12], which can undermine the credibility of academics’ recommendations on climate change [13]. Nonetheless, attending in-person scientific conferences continues to be strongly encouraged and often linked to academic excellence [7, 8, 14–16].

### Strategies for changing Academia’s practices and behaviours: *Hard* and *soft* levers

Increasingly, universities and research centres (National Centre for Scientific Research [17], EHT Zurich [18]), communities of actors from the academia (Ma Terre en 180 minutes community [19], Labo1point5 community [20]) and international conference organisers [21] are committing to proposing strategies to reduce the carbon footprint of the academic world.

In this study protocol, strategies will be categorised in *Hard* levers and *Soft* levers [22–24]. *Hard* levers aim to change the economic and geographical contexts of individuals to encourage or discourage them from adopting a practice. In general, *hard* levers seek to build enabling environments for the adoption of behaviours [25]. In recent years, in the Academic context, *hard* levers as economic (dis)incentives (e.g., carbon tax on air travel [26]), limiting air travel by applying individual or collective quotas [27, 28], replacing air travel by videoconference [7], prohibiting air travel (e.g., for domestic air travel or for easily achievable travel by train) and making it more complicate (e.g., longer procedures) to purchase airline tickets [29] have only started to be implemented.

*Soft* levers or behavioural interventions aim to change the psychological factors associated with behaviours, such as the intention to reduce air travel for professional mobility and subjective norms (the feeling of social pressure to adopt a practice deemed acceptable or expected by others). In general, *soft* levers seek to influence attitudes, motivations and reasons for adopting a practice [30]. In the field of behaviour change literature, these levers are referred to as behaviour change techniques [31]. Some examples of behaviour change techniques in the field of academic behaviours are the creation of tools to inform about the emissions of air travel [29], relaying detailed documents about how to travel in a train or engaging in eco-friendly actions during conferences (e.g., [21]), informing about the social and environmental impacts of air travelling [9], developing and promoting the use of collaborative workshops and serious games to raise awareness and discuss transition pathways [19]. Indeed, serious games are becoming increasingly widespread to promote pro-environmental behaviours and climate change adaptation behaviours [for reviews, read 32–34]. Although the use of serious games can influence the perception of climate change issues, stimulate cognitive engagement and even increase the intention of adopting new behaviours [32, 33], most of them present similar limitations [32]. First, most studies examine and evaluate the gains in knowledge and participants’ engagement without measuring any actual behavioural changes. Second, they often lack of rigorous methodologies including controlled designs (i.e., comparing the effects of an experimental group containing a serious game versus a control group containing other content or no content at all) and longitudinal designs (i.e., studies following the participants’ behaviours and knowledge over weeks or months). Third, to our knowledge, there is a lack of studies taking into account the socio-spatial context of the individuals who participate in serious games (their age, their socio-economic status, the characteristics of their living areas). Ma Terre-EVAL study aims to address all the aforementioned limitations.

### Ma Terre-EVAL pilot study

Ma Terre-EVAL is a study carried out by a consortium of researchers in social psychology, human geography and climate science aiming to better understand the motivations and obstacles to adopt ecological transitions paths in Academia. For this purpose, Ma Terre-EVAL combines concepts and knowledge in climate science, gaming and simulation, human geography and behavioural sciences to evaluate the effects of a serious game on three academic practices: professional mobility by air, daily commuting by car and digital and material purchases. Moreover, the motivations towards changing behaviours and the socio-economic and institutional contexts will also be assessed. Ma Terre-EVAL will rely on rigorous methodologies such as a randomised controlled study comparing an experimental arm versus a control arm, a longitudinal follow-up of 6 weeks spread over 24 months and a large-scale study with 1000 participants. More precisely, the sample size was estimated by using *a priori* sample calculation in G*Power 3.1.9.4 [35, 36] by considering that implementing *soft* levers in our second dependent variable (because no study has investigated the effects of *soft* levers on air travel) reduces 7% of daily travel by car (*g* = 0.16, Z = 6.419, p < .001, 95% CI [0.113, 0.213], [37] and considering a significance level of 0.05 and a statistical power of 80%. The behaviours of Academia’s actors will be assessed through detailed online surveys (e.g., questionnaires about the numbers of academic travels, distances travelled and questionnaires assessing intentions, habits, subjective norms and socio-economic and institutional contexts).

The main objective of this pilot study will be to evaluate the feasibility and the fidelity of Ma Terre-EVAL study through a shorter version (a follow-up of two weeks over one month and a half) with a small number of participants. In this study, the feasibility will be understood as the extent to which the different elements of the intervention and evaluation are feasible for the implementation team [38] and the fidelity will be understood as the extent to which all the elements of the intervention are accurately implemented and without modifying the behaviour change techniques and contents [39]. For evaluating the feasibility and the fidelity of this study, a 1-month and a half pilot randomised controlled trial, parallel groups, two arms, exploratory trial with a 1:1 allocation ratio will be implemented. More precisely, the objectives of the study are twofold:

Evaluate the feasibility of the different elements of the interventions (completion or non-completion of planned tasks, assessment of task complexity, participation rates in intervention sessions) and the evaluation (completion rate of online questionnaires and quality of the responses) proposed in Ma Terre-EVAL study.Evaluate the fidelity of the behavioural interventions provided to the experimental and control arms (the extent to which all the different elements of the interventions and evaluation are feasible for the team implementing the study).

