### Outcomes and data collection

#### Primary outcomes and data collection methods

The main outcomes of Ma Terre-EVAL pilot will be the feasibility of the intervention, the feasibility of the evaluation of behavioural changes and the fidelity of the intervention.

The intervention’s feasibility will be operationalised in three variables: 1) Task completion (a checklist of all activities that need to be carried out during the intervention sessions), 2) Complexity of the intervention tasks (a scale of 1 to 3, from easy to difficult) and 3) Percentage of participation in the meetings (percentage of people absent or present at the intervention meetings). All of this information will be collected through paper questionnaire.

The feasibility of the evaluation of behavioural change will be operationalised in two variables: 1) Completion rate of the online questionnaires (average of the completion of each questionnaire) and 2) Quality of the answers (considering the duration of each questionnaire). More precisely, the quality of the answers will allow us to detect participants who potentially do not take the task seriously enough (i.e., with unrealistic short time on certain tasks) by calculating the Median Absolute Deviation [46] to detect outliers on the time spent on the page showing the article and will exclude participants with a Median Absolute Deviation superior to 3. Both of these outcomes will be calculated by the scientific team by downloading the online surveys completed by the participants of the study.

Finally, the fidelity of the intervention will be operationalised in two variables: 1) Exposure to the intervention (average time of each session) and, 2) Responsiveness of the participants (via a scale of 1 to 7 from not at all responsive to very responsive, this question will be asked to each facilitator). All of this information will be collected through paper forms. All the details of the variables, tools and measurement times can be found in Table 2.

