#### Statistical methods

*Analysis of the feasibility of the intervention and adherence*. Concerning the Task completion, we will identify the tasks that were not completed (i.e., for each group of participants and for each meeting) and we will calculate the percentage of completion of each task (e.g., the discussion about planetary limits was completed in 100% of IM_1_ for experimental and control arms). Concerning the perceived complexity of tasks, we will calculate the average complexity of each task (from 1 to 3) and look at all the comments noted by the facilitators. Concerning the adherence, a participation/absence rate will be done per each intervention meeting.

*Analysis of the feasibility of evaluation*. Concerning the Completion rate of online surveys, we will calculate the percentage of completion of online questionnaires during the first session of measurement (S_0_) and the second session of measurement (S_1_). Concerning the quality of the responses, we will calculate the Median Absolute Deviation [46] to detect outliers that spent too few or too much time to complete the surveys (participants with a Median Absolute Deviation > 3).

*Analysis of the fidelity of the intervention*. Concerning the exposure to the intervention, we will calculate the average duration of each intervention meeting. Concerning the perceived responsiveness of participants, we will calculate the average of perceived responsiveness per each intervention meeting.

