Because of the complexity of the interventions proposed to the experimental and control arms and the complexity of the evaluation of the behavioural changes, this pilot randomised controlled trial aims to evaluate the feasibility (the extent to which all the different elements of the interventions and evaluation are feasible for the team implementing the study) of the intervention and the evaluation of the fidelity (the extent to which all the elements of the intervention are accurately implemented and without modifying the behaviour change techniques and contents). Indeed, several authors [39, 47, 48] have indicated that every large-scale study should be pre-tested with small groups of participants to identify elements that could be adapted to ensure better feasibility and fidelity.

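### Objective 2 explains fidelity in feasibility terms, and the two fidelity outcomes measure session length and engagement, not delivery of the planned elements

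*Protocol article*

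**What the plan says.** **Definitions.** The Background section on the pilot study separates two ideas before it lists the objectives. Feasibility is "the extent to which the different elements of the intervention and evaluation are feasible for the implementation team". For fidelity, "the fidelity will be understood as the extent to which all the elements of the intervention are accurately implemented", with the added condition that techniques and contents are not altered. Objective 2 then reads "Evaluate the fidelity of the behavioural interventions provided to the experimental and control arms (the extent to which all the different elements" and completes the bracket with the feasibility idea: "the extent to which all the different elements of the interventions and evaluation are feasible for the team implementing the study". The Discussion uses the same words for the other concept, "feasibility (the extent to which all the different elements of the interventions and evaluation are feasible for the team implementing the study", and keeps for fidelity the meaning that "all the elements of the intervention are accurately implemented and without modifying the behaviour change techniques and contents". The Abstract likewise describes fidelity as agreement between implementation and design.

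**Outcomes and analysis.** Table 2 and the primary outcomes section give fidelity two variables. The first is "Exposure to the intervention (average time of each session"; the second is participants' responsiveness, scored 1 to 7 by the facilitator. Under Statistical methods the exposure analysis is that "we will calculate the average duration of each intervention meeting", and responsiveness is averaged per meeting. The checklist of session activities is listed and analysed under feasibility of the intervention.

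**Related material.** The timeline section says that the tables filled in by facilitators serve to evaluate both fidelity and feasibility. The Adherence section has facilitators note meeting durations and anything that disrupts the planned elements.

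**The concern.** Fidelity is one of the pilot's two main objectives, and the pilot is meant to inform a 24-month trial with 1000 participants. The arms differ only in the second meeting, where the serious game is played. The larger trial therefore needs to know whether that meeting, and the first meeting shared by both arms, were delivered as designed.

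A fidelity conclusion drawn as the article lays it out would rest on two averages that carry no information on content. A game session of the planned length with lively players would score well on both, even if the guided negotiation or the debriefing had been left out. The omission would appear in the report, but under feasibility, and the stated fidelity analysis would not draw on it. The wording of objective 2 adds to the problem, because it tells the reader to judge fidelity by whether the work was manageable for the team.

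**Working it through.** The article gives no figure to reproduce on this point. The check is a comparison of texts plus two short calculations.

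**1. Definitions side by side**

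| Place | Meaning given to fidelity |
|---|---|
| Abstract | implementation matches the design |
| Background, before the objectives | accurate delivery, techniques and contents unaltered |
| Background, objective 2 | elements feasible for the team |
| Discussion | accurate delivery, techniques and contents unaltered |

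Objective 2 is the outlier against three other statements. Its bracket matches word for word the phrase that the Discussion attaches to feasibility. It also takes in the evaluation, which is no part of the fidelity of an intervention.

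**2. What each variable can show**

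| Variable | Filed under | Shows which elements were delivered? | Shows whether they were altered? |
|---|---|---|---|
| Mean session duration | fidelity | no | no |
| Facilitator-rated responsiveness | fidelity | no | no |
| Task checklist | feasibility | yes | not as described |
| Notes on disruptions | adherence | in part | possibly |

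The two variables under fidelity are the two that say nothing about content.

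**3. Number of sessions.** The inputs are N = 30 (power and sample size section), 1:1 allocation, and groups of five (Experimental arm and Control arm sections).

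- Groups per arm: (30 / 2) / 5 = 3.
- First meetings: 3 × 2 = 6. Second meetings, experimental arm only: 3.

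This assumes full recruitment and full groups. The duration averages would then rest on three to six sessions.

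**4. Cancellation in the mean.** The planned lengths are 1 hour = 60 minutes and 2 hours 20 minutes = 140 minutes. As an illustration with assumed values, take three game sessions of 110, 140 and 170 minutes.

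- Mean: (110 + 140 + 170) / 3 = 420 / 3 = 140, exactly the planned length.
- Departure of the first and third: 30 / 140 = 21% each.

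Two of three sessions are clearly off plan and the summary shows none of it. The analysis text states no comparison with 60 or 140 minutes.

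**The case against.** The strongest reply is that this is a matter of wording and filing. The right definition appears three times, the faulty bracket has one obvious correction, and no outcome or analysis is derived from it. Content delivery is measured: the checklist covers the activities planned for the sessions and is itself a main outcome. The facilitator tables are expressly meant for both concepts, and disruptions are noted. Session length is partial evidence of delivery as designed, since the planned lengths are fixed. Duration is recorded for each session, so individual values will be in hand. The 110/140/170 example is invented, and details such as spread or tolerance may sit in a fuller plan that is not shown.

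Much of this stands, and it rules out two stronger readings:

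- A reader might infer that objective 2 cannot be answered at all. The documents do not support that, because the checklist and the disruption notes supply relevant data.
- A reader might infer from the example under Statistical methods that task completion will be pooled over arms and so conceal a shortfall in one of them. The same paragraph first has uncompleted tasks identified by participant group and by meeting, so such a shortfall would be found.

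The reply does not remove the mismatch. The article states which variables make up fidelity and how they are analysed, and the checklist is in neither list. That is a choice made in the text, not a detail left open. The statement that the forms serve both purposes makes the omission an inconsistency.

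**Conclusion.** The point holds, at moderate weight. Objective 2 contradicts the article's own definition of fidelity, and the variables assigned to fidelity capture dose and engagement, not delivery of the planned elements. The data for most of the repair are already to be collected, so the defect lies in what the fidelity conclusion is based on, not in what is measured.

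The size cannot be put as a single number. The fidelity averages would rest on about six first meetings and three game sessions, and the illustration shows that a mean equal to plan is compatible with two of three sessions being 21% off. The session counts assume 30 participants in full groups of five; the durations are assumed values.

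One limit remains. The checklist as described records whether a task was completed, not whether its content was changed, so on its own it does not cover the whole of the article's definition. The facilitator tables are not shown, so it cannot be judged whether they already record changes.

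**What to change.** - **Objective 2:** replace the bracket with the fidelity definition given in the Discussion.
- **Fidelity outcomes:** use task completion as a fidelity outcome as well as a feasibility outcome, reported as counts by session and by arm, together with the disruption notes described under Adherence. Keep responsiveness as supportive information.
- **Duration:** list each session's length beside the planned 60 or 140 minutes, instead of giving only the mean. With about nine meetings in all (6 + 3), this is one short table. A tolerance band (10%, for example) and tagging checklist items with their behaviour change technique codes are optional.
- **Alteration of content:** if the form has no such mark, add one for elements delivered with changes. Otherwise, limit the fidelity conclusion to completeness of delivery.

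The cost is one corrected bracket and some re-tabulation of data already planned, plus at most one extra mark on an existing form.
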